#### Secondary aims

2.4.2

A set of complementary outcomes will also be assessed to broadly characterize the impact of each exercise intervention, including: body composition, strength, functional performance and overall GM composition. All the methods, instruments and protocols are fully detailed in next sections.

### Assessments

2.5

Participants will be evaluated in three different moments: (i) baseline; (ii) end of the intervention (12 weeks); (iii) close-out (24 weeks). The study has a total duration of 26 weeks. In each study visit, participants will perform the same physical and functional assessments, body composition analysis, and provide a fasting blood and feces sample. Other confounding variables will also be recorded, including nutritional intake (through a 3-day diary), daily PA levels (through a PA tracker), medication intake. Medication and supplementation along with other associated comorbidities will be assessed using a medical questionnaire and medication history questionnaire. Considering the study design, the following outcomes will also be evaluated: (a) retention and attrition rates; (b) adherence to exercise intervention; (c) safety; (d) intervention effect on dependent outcomes (Table 4).

**Table 4 tab4:** Overview of the assessment visits and data collection at each visit.

Study phase	Pre-randomization		Intervention		Follow-up
Visit description	Screening	Baseline	Start	End	CO
Visit number	1	2	3	4	5
Week number	−2	0	2	14	26
Informed consent, review inclusion/exclusion criteria	x				
Demographic information, medical history, medication use	x				
IPAQ questionnaire	x				
Office blood pressure	x	x	x	x	x
Anthropometry measurements	x	x		x	x
Randomization	x				
Body composition (DEXA)		x		x	x
Blood and fecal samples for study assays		x		x	x
Nutritional Intake		x		x	x
Skeletal muscle strength		x		x	x
Physical performance testing		x		x	x
Daily physical activity		x	x	x	x
Assess adverse events			x	x	x
Exercise intervention			x	x	

CO, close-out.

#### Biospecimen collection—microbiome and metabolomics

2.5.1

At each assessment visit, whole blood and fecal samples will be collected to assess: (a) GM composition and function, i.e., abundance of *Faecalibacterium prausnitzii* and other SCFA-producing bacteria after the intervention; *Lactobacillus* and Bifidobacterium genera after the intervention and at the end of follow-up; relative abundance and diversity at different taxonomic levels such as *Bacillota (Firmicutes)* and *Bacteroidetes* and *Bacteroidetes/Bacillota* ratio; (b) systemic gut-derived metabolites. Venous blood samples will be collected after a fasting period of at least 8 h. These biospecimens will be collected in the morning, between 8 and 10 am in two 5 mL blood tubes. Whole blood will be separated through a centrifugation process for plasma and serum separation, which will be then aliquoted and stored at −80°C for metabolomic assays.

##### Microbiome

2.5.1.1

Fecal samples will be collected at all assessment visits. Participants will receive a kit composed of: (a) 3-day dietary log record; (b) a fecal collection kit (EasySampler, GP Medical Devices, Holstebro, Denmark); a stool collection tube with DNA stabilizer (Invitek Diagnostics, Berlin, Germany); and (c) instructions to take home about the collection and transportation process. The collection tube has a DNA preservative solution that guarantees the biospecimen integrity for several weeks at room temperature. Samples will be extracted using the PSP Spin Stool DNA Basic Kit from Invitek Diagnostics and GM composition will be analyzed through metabarcoding of fecal samples using high-throughput next generation sequencing (NGS) of amplicon libraries of the V3-V4 region of the 16S rRNA, using the Quick-16S Plus NGS Library Prep Kit (V3-V4, UDI), from Zymo Research (Irvine, CA, United States).

##### Metabolomics

2.5.1.2

Systemic gut-derived metabolites will be assessed on serum samples using an untargeted liquid chromatography- mass spectrometry (LC–MS) approach, which will quantify circulating metabolites using the Thermo Q-Exactive Orbitrap mass spectrometer with Dionex UHPLC and autosampler. All samples will be analyzed in positive and negative heated electrospray ionization with a Time-of-flight (TOF) survey scan from m/z 50–1,000 collected at 4 Hz throughout each LC–MS run.

#### Skeletal muscle function

2.5.2

Dominant lower limb knee extension and flexion muscle strength will be assessed through an isokinetic dynamometer, the Biodex System 3 Pro isokinetic dynamometer (System 4 Pro™, Biodex Medical Systems, Shirley, New York, United States) at baseline, end of intervention and close-out. The isokinetic dynamometer is the gold standard method for muscle strength assessment, allowing precise evaluation of force generation within a pre-established range of motion and speed. Test parameters will be defined according to the manufacturer instructions, namely: 90° dynamometer orientation, 0° tilt, 90° seat orientation, 80° seatback tilt and axis of rotation aligned with the lateral femoral condyle determined by inspection and palpation. Participants will be asked to avoid strenuous physical activities in the 48 h prior to testing. Participants will complete a 1 min warm-up consisting of leg extensions and flexions without load while seating in the equipment chair. Afterwards, participants will be fixed to the equipment chair with straps and a passive knee flexion starting from 0° extension will be performed to assess leg weight for gravity correction purposes. Participants will then perform two training sets of 5 reps of isokinetic extension/ flexion at 60°/s, between 0 and 90° range, with a 30s rest interval between sets. After 2 min rest, patients will perform two testing sets of 5 reps with 90s rest interval between sets. Patients will perform the test by exerting maximum possible pressure on the isokinetic arm throughout the entire range of movement. Standardized instructions will be given to encourage maximal muscle performance throughout the test. Peak torque of extension and flexion total work (J) obtained throughout the test in each valid set will be recorded. Maximal muscle strength will be defined as the highest peak torque (Nm) obtained. To avoid sub-maximal performance or outliers, if the peak torque coefficient of variation between the 3 best testing sets exceeds 15%, a new testing set will be performed until a lower than 15% coefficient of variation is obtained between 3 sets. Non-dominant handgrip strength will be assessed using a hand dynamometer (Jamar Plus+ Digital Hand Dynamometer) with participants seated, shoulder adducted in neutral rotation, arm at the side of the body and elbow flexed at 90°. Participants will be encouraged to exert their maximum grip strength. Three repetitions of 3 s will be performed with 30 s interval. The average value of the two repetitions with the lowest coefficient of variation will be considered.

#### Anthropometry and body composition

2.5.3

Body weight (BW) and height will be measured using a precision scale coupled to a stadiometer (Seca 285). The Body Mass Index (BMI) will be calculated using the BMI = weight/height^2^ equation. Waist and hip circumferences will be measured with a measuring tape (Seca 203) according to WHO guidelines (33), and then waist-to-hip and waist-to-height ratios will be calculated. Body composition and percentage body mass will be assessed by whole-body DXA (DXA; Hologic Explorer QDR) according to the manufacturer recommendations and using standard protocols for positioning and analysis of the DXA scans. The same DXA equipment will be used throughout the experimental period. All scans will be performed and analyzed by the same trained researcher. Phantoms will be scanned daily, and coefficients of variation will be analyzed during the experimental period to ensure reliability. In every assessment (baseline, end of the intervention, and close-out) each participant will perform a whole-body scan for total and regional body composition. The outcome variables obtained with DXA are total and regional lean mass (kg, %), total and regional fat mass (kg, %), absolute appendicular skeletal muscle mass, relative appendicular skeletal muscle mass per weight, height and BMI. All participants will be assessed between 8 and 10 am following a > 8 h fasting period while wearing only light cloths. For whole-body composition assessment, participants will lie supine with arms alongside, legs in extension and slight internal rotation with feet attached by a Velcro strap. Anthropometric measurements and body composition will be assessed using appropriate procedures and gold standard methods.

#### Nutritional intake

2.5.4

All participants will be instructed to record their total food and drink intake during the three consecutive days prior to the day of fecal collection using a food diary. At each of the three scheduled assessment visits (baseline, end of the intervention and close-out), all participants will receive a small brochure, with pre-printed forms, in which they will record the information about the time, type and amount of food and beverages consumed. Together with the delivery of the diary, participants will receive instructions with an explanation and practical examples on how they should record this information. After the 3 days of recording, participants will return the diary booklet (together with the fecal collection sample). The first A5 size booklet, will be delivered in the subsequent experimental periods to help standardize the nutritional intake. This will aid in the analysis of other parameters, since differences in fiber, protein and total energy intake between groups may significantly interfere with the interpretation of the primary and secondary outcomes. After all nutritional data has been collected, food intake will be encoded, and a comprehensive nutrient analysis will be performed with the Food Processor Plus software (ESHA Research).

#### Physical performance

2.5.5

The physical performance of the participants will be evaluated at baseline, end of the intervention and at close-out using gait speed, the 30-s chair rise, the Short Physical Performance Battery (SPPB) and the 400 meter walk test as recommended by the EWGSOP guidelines (27). To assess gait speed, we will use the 4-m usual walk test with speed time measured with a stopwatch. A cut-off speed ≤0.8 m/s is an indicator of severe sarcopenia while 1.0 m/s is a sign of physical function limitations. The 30-s chair rise test counts how many times a participant can rise and sit in the chair over a 30-s interval and evaluates lower limb strength and endurance. The SPPB is a composite test battery that includes assessment of gait speed, a balance test, and a chair stand test. Each test is scored 4 points until a maximum score of 12 points. In contrast a score of ≤8 points indicates poor physical performance. Lastly, in the 400-meter walk test, participants are asked to complete 20 laps of 20 m, each lap as fast as possible, and are allowed up to two rest stops during the test. This test evaluates walking ability and endurance. These tests are expressed in a continuous quantitative scale that allows the assessment of longitudinal changes gradually over time (improvements or decline). Participants will be evaluated between 8 and 10 a.m. and will be instructed to avoid vigorous exercise in the 2 h prior to testing to minimize intraday variability, temperature effects, and biological rhythms. In addition, participants will be asked to wear comfortable clothes and appropriate walking shoes and to continue their usual medication. The recommended reasons to stop the physical performance testing included: chest pain, intolerable dyspnea, leg cramps, staggering, diaphoresis, and pale or ashen appearance. Participants will be evaluated in the same testing order: (1) gait speed (m/s); (2) the SPPB (score); (3) 30-s chair rise (count); and (4) the 400-m walk test (s).

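### The 400-m walk is defined only as seconds over a fixed distance, so a participant who stops early has no value, and the value is missing because of poor performance

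*Protocol article*

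**What the plan says.** All of the following is in section 2.5.5 (Physical performance) of the protocol article unless stated otherwise.

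- The task is a fixed distance: "participants are asked to complete 20 laps of 20 m, each lap as fast as possible", that is 20 × 20 m = 400 m. Participants "are allowed up to two rest stops during the test".
- The unit is seconds. The testing order ends with "and (4) the 400-m walk test (s".
- Testing can end early: "The recommended reasons to stop the physical performance testing included: chest pain, intolerable dyspnea, leg cramps, staggering, diaphoresis, and pale or ashen appearance".
- The section claims for the whole battery: "These tests are expressed in a continuous quantitative scale that allows the assessment of longitudinal changes gradually over time".
- Section 2.4.2 makes functional performance one of several complementary outcomes: "A set of complementary outcomes will also be assessed to broadly characterize the impact of each exercise intervention". The hypotheses at the end of section 2.6 expect better physical performance in the concurrent arm.
- Section 2.6 plans mixed models for the main analyses and states intention to treat for the primary outcome only.

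The article does not say what is recorded for a walk that ends before 400 m, whether rest time counts, or what follows if a third rest is needed. It gives no non-completion rate.

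**The concern.** A time over 400 m exists only for someone who covers 400 m. For a participant stopped at lap 12, the continuous scale that section 2.5.5 claims has no entry, and the reason is the very limitation the test is meant to measure. The other three tests do not depend on covering a long distance: the SPPB is a score, the chair rise is a count and gait speed needs 4 m.

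Two things are at stake. First, if training in one arm lets more weak walkers finish, that arm's recorded times include slow finishers whose counterparts in the other arm are missing, so a real benefit looks smaller. Second, if laps and the reason for stopping are not written down at the visit, no later analysis plan can recover them. Section 2.4.1 presents the pilot as a way to refine procedures for a full-scale trial, so the completion rate is itself useful information.

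**Working it through.** **Plan's own figure.** The article gives none for the walk. Its sample size of 21 per group (section 2.2.2: d = 0.9, 80% power, two-sided 0.05, for *F. prausnitzii*) reproduces with the noncentral t: power is 79.2% at 20 and 81.2% at 21. It is used below only as a group size.

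**Text side by side.** Seconds over 400 m, plus permitted early stopping, plus no rule for a stopped walk, gives no value for a stopped walk. A mixed model uses every observed visit, but it assumes that whether a visit is missing depends only on observed data. Here it depends on the unobserved walking ability at that visit.

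**Illustration 1: walking speed, one visit, finishers only.** Assumptions, none from the documents: speed is normal with SD 0.25 m/s, the means are 1.00 and 1.10 m/s (true difference 0.10), and anyone below a threshold speed c does not finish. The mean among finishers is μ + σ·φ(a)/(1 − Φ(a)), with a = (c − μ)/σ.

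For c = 0.7:
- Weaker arm: a = −1.2, mean 1.00 + 0.25 × 0.1942/0.8849 = 1.055.
- Stronger arm: a = −1.6, mean 1.10 + 0.25 × 0.1109/0.9452 = 1.129.
- Difference: 0.074.

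| c (m/s) | Non-finishers, weaker / stronger arm | Difference among finishers | Loss |
|---|---|---|---|
| 0.6 | 5% / 2% | 0.084 | 16% |
| 0.7 | 12% / 5% | 0.074 | 26% |
| 0.8 | 21% / 12% | 0.063 | 37% |

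**Closer to the planned analysis.** The same scenarios in a two-visit likelihood model, with a common baseline mean and an assumed within-person correlation of 0.7 to 0.9, give a loss of about 5% to 27%. Baseline values recover part of the information, so the table is an upper illustration.

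**Illustration 2: effect on power.** Assumptions: standardised time with SD 1, true d = 0.9 (borrowed from the primary outcome), a fraction p of the comparator arm beyond the cut-off t, 21 per group, one visit. The difference among finishers is d − [λ(t) − λ(t + d)], with λ = φ/Φ. For p = 10%, t = 1.282, and 0.9 − (0.195 − 0.037) = 0.742. For p = 20%, t = 0.842, and 0.9 − (0.350 − 0.091) = 0.641. Power is simulated with 4,000 repeats; in the rank test all non-finishers tie at worst.

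| p | Share of d kept | Power, finishers only | Power, non-finishers ranked worst |
|---|---|---|---|
| 5% | 90% | 76% | 80% |
| 10% | 82% | 70% | 79% |
| 20% | 71% | 60% | 78% |
| 30% | 62% | 51% | 78% |

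With complete data, power is about 81%. With no true difference, the difference among finishers is about 0 and the type I error stays near 5%. With p close to 0 there is no loss. In a group of 23, one non-finisher is 1/23 = 4% and three are 13%.

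**The case against.** The strongest reply is that this is detail a journal article leaves to a test manual, full protocol or analysis plan. Such a rule may exist, and the missing rule alone would not be a finding. What remains is that the article positively fixes the unit as seconds and claims a continuous scale, which cannot hold for a walk that was stopped. The remedy also concerns what is captured at the visit, which a later analysis plan cannot supply.

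A second reply is that few may fail to finish. Volunteers come from a community exercise program, section 2.2.1 excludes many cardiac, respiratory and musculoskeletal conditions, and slow gait and low SPPB appear there as severity grading next to the grip and muscle-mass criteria. This stands: the rate could be low. It is not known to be low, because the walk is done at screening (section 2.2) but section 2.2.1 sets no requirement to complete it.

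Readers might also infer more than the documents support:

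- **That the endpoint is biased as planned.** This needs non-finishers and a true difference between arms. Neither is established.
- **That a third rest ends the test.** Section 2.5.5 allows up to two rests and does not say what happens next. The stopping reasons are called recommended and apply to the whole battery.
- **That anyone who misses one visit is lost.** This would follow from a change-score analysis. The planned mixed models keep each observed visit, so the one-visit losses overstate the effect.
- **That average speed over the distance covered would solve it.** Someone who stops early after a fast start could score above a slower participant who finishes.

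**Conclusion.** The point holds in a limited form. Section 2.5.5 leaves a stopped walk without a value, for a reason tied to performance, and the planned models would treat that value as missing at random. If non-completion is not negligible and the arms differ, the estimated difference shrinks toward zero. The size cannot be taken from the documents. With weaker-arm non-completion of 5% to 21%, normal speeds and a single threshold for not finishing, the loss is about 5% to 27% in a two-visit likelihood model and at most about 16% to 37% in a one-visit comparison of finishers. It is zero if everyone finishes or the arms do not differ, and a false positive is not made more likely in the latter case. The issue is confined to one complementary outcome of a pilot trial. It is worth correcting because the remedy is cheap and the data cannot be recovered afterwards.

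**What to change.** At baseline, end of intervention and close-out, record for each 400-m walk the laps completed, the elapsed time including rests, completion (yes/no) and the reason for stopping. In section 2.5.5, say that seconds apply to participants who finish and that rest time counts.

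In section 2.6, keep the analysis of seconds for finishers and add a rank-based comparison between arms in which non-finishers rank below all finishers and are ordered among themselves by distance covered. Report completion by arm and visit. A participant who does not attend the visit remains missing and is not ranked as a non-finisher. Do not replace time by average speed over a truncated distance. No stopping or rest rule needs to change.

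The cost is a few form fields, two or three sentences and one extra analysis. The rank result is less directly interpretable than a difference in seconds, which is why both should be reported.

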#### Additional assessment procedures

2.5.6

Per the study design, we will also evaluate: (a) retention and attrition rates; (b) adherence to exercise intervention; (c) safety. The success of recruitment and retention rates will be measured by the number of participants recruited, the number of drop-outs and losses to follow-up throughout the trial. To consider a dropout, the participant must miss at least two consecutive training weeks (*n* = 6 training sessions) without any explanation nor successful contact from the study team. Adherence to the exercise intervention will be carefully documented by study staff and will be measured by the number of sessions attended. Safety will be measured by the number and/or seriousness of adverse events attributable to the intervention and will be monitored and recorded by study staff throughout the trial.

The clinical and medication history will be assessed by the General Health and Physical Activity Questionnaire, an adapted version (34). This questionnaire will also collect the smoking habits and participants’ demographic information. Office BP will be assessed on the left arm after 5 min rest, in the seated position with a digital sphygmomanometer (Efficia, CM150, Philips). Physical inactivity will be assessed by the IPAQ – Portuguese version. Participants with ≤150 min/week of moderate PA or without regular exercise training habits will be classified as physically inactive (35).

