**Figure 1 fig1:**
[figure not shown]
Descriptive scheme of the study flow and assessments.

Exercise intensity during the sessions will be measured using heart rate (HR) monitors and using the Borg Perceived Exertion Scale (30) across the different groups. The exercise interventions followed the *Consensus on Exercise Reporting Template* (CERT) guidelines (31). All instructors will undergo thorough training to standardize protocols prior to study beginning. All adverse events that occur during the exercise sessions will be recorded. When participants miss two consecutive sessions, they will be contacted by their instructor for support and evaluation. Motivational text messages will be sent to all participants to encourage their continued involvement. Although no other home exercise intervention will be provided to the experimental groups, daily home PA will be assessed in all groups using the FitBit^®^ Zip (San Francisco, CA, United States), and sedentary time, light, moderate and vigorous PA, and step count will be recorded—these data will serve as a covariate in the analysis of the primary outcome. Participants will be discontinued from the exercise intervention if significant adverse events occur [i.e., major cardiovascular (CV) events, hospitalization, major musculoskeletal injury, death or other life-threating situation] or if they engage in another structured exercise intervention (Figure 2).

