#### Primary aim

2.4.1

The primary outcome is to assess the change in the relative abundance of *Faecalibacterium prausnitzii* and other SCFA-producing bacteria after the intervention (12 weeks). The change in the relative abundance of *Faecalibacterium prausnitzii* was selected as the primary aim given that, to date, there are no studies of exercise effect on GM nor a consensual marker of microbiome health status in these patients (32), and thus, the preliminary data collected in this study, will help us to refine our sample size and study procedures for a full-scale RCT. In addition, it has been shown that patients with sarcopenia have decreased abundance of this bacterial strain- a known SCFA-producing bacteria, with an important role on systemic inflammation, anabolic resistance, insulin sensitivity, and energy production (5, 15). Secondary outcomes are the change in relative abundance of *Faecalibacterium prausnitzii* at close-out (24 weeks), the change in the relative abundance of the genera Lactobacillus and Bifidobacterium after the intervention and at the end of follow-up.

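### The dropout rule omits explained exits and the safety measure keeps only attributable events, so reported attrition and harm may be understated by an amount that cannot be computed.

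*Protocol article*

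**What the plan says.** Section 2.5.6 measures recruitment and retention by "the number of participants recruited, the number of drop-outs and losses to follow-up throughout the trial". It then defines the dropout: "To consider a dropout, the participant must miss at least two consecutive training weeks" (six sessions), "without any explanation nor successful contact from the study team". Loss to follow-up is not defined. Adherence is counted separately, as sessions attended.

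Section 2.3 has the instructor contact anyone who misses two sessions in a row. It also says "Participants will be discontinued from the exercise intervention if significant adverse events occur", giving as examples major cardiovascular events, admission to hospital and major musculoskeletal injury, and it applies the same to people who take up another structured exercise programme.

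On safety, Section 2.5.6 says "Safety will be measured by the number and/or seriousness of adverse events attributable to the intervention", monitored for the whole trial. Section 2.3 says "All adverse events that occur during the exercise sessions will be recorded". Table 4 has a row "Assess adverse events" marked at start, end and close-out. Section 2.2.3 explains that participants and instructors cannot be blinded.

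Section 2.2.2 allows 10% attrition, going from 21 to 23 per group. Section 2.4.1 says the preliminary data "will help us to refine our sample size and study procedures for a full-scale RCT".

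**The concern.** A dropout must meet every condition at once: two missed weeks, no explanation and no contact. The exits that say most about how tolerable a regimen is, such as injury, illness or finding the programme too demanding, normally come with an explanation. In a comparison of three exercise regimens these are also the exits most likely to differ by arm. A rule that removes them can make the regimens look equally well retained when they are not.

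The safety measure has a similar filter. An event must be judged attributable before it counts, and those closest to the sessions know the arm.

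Attrition and safety are listed outcomes of the pilot. If the reported figures are too favourable, anyone planning a larger trial from them would start from too low an attrition rate and an incomplete picture of harm.

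**Working it through.** **1. Who the dropout rule leaves out.**

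| Exit | Dropout under Section 2.5.6? | Counted elsewhere? |
|---|---|---|
| Stops attending, cannot be reached | Yes | – |
| Says they are withdrawing | No (explained) | Only if treated as lost to follow-up |
| Misses sessions, reached by staff, does not return | No (contacted) | As above; also low attendance |
| Discontinued under Section 2.3 | No (explained) | As above; also low attendance |
| Leaves during the 12-week washout | No (no sessions to miss) | Only as lost to follow-up |

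Contact is attempted after two missed sessions, while the rule needs six. The trial's own follow-up procedure therefore moves reachable people out of the dropout count. Someone who stops exercise with a reason but still attends visits is neither a dropout nor naturally lost, and appears only as poor attendance.

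**2. What the attrition allowance refers to.** The plan's figure reproduces. With d = 0.9, two-sided alpha 0.05 and 80% power, a two-sample t calculation (noncentral t) gives 21 per group, power 0.812. For 10% attrition, 63/(1 − 0.10) = 70 and 63 × 1.10 = 69.3, against the stated 69. This is not in dispute. It shows that 21 is the number needed for analysis, so the 10% is a rate of missing endpoints. Dropout is defined on attendance. The two can differ either way: a person may stop training and still give the stool sample, or train throughout and not give it.

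**3. Size, on assumed values only.** The documents give no observed attrition and no split by reason. Assume true attrition of 10% to 25%, and that 25% to 75% of exits fall outside both counts.

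Counted attrition = true attrition × (1 − share not counted).
Planned per arm = 21/(1 − counted attrition), rounded up. Needed per arm = 21/(1 − true attrition), rounded up.
Power is for d = 0.9 at the whole number of completers, planned × (1 − true attrition).

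| True attrition | Share not counted | Counted | Planned / needed per arm | Power |
|---|---|---|---|---|
| 10% | 25%, 50%, 75% | 7.5%, 5.0%, 2.5% | 23, 23, 22 / 24 | 0.79, 0.79, 0.77 |
| 20% | 25%, 50%, 75% | 15%, 10%, 5% | 25, 24, 23 / 27 | 0.79, 0.77, 0.75 |
| 25% | 25%, 50%, 75% | 18.75%, 12.5%, 6.25% | 26, 24, 23 / 28 | 0.77, 0.75, 0.72 |

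A later trial planned on the counted rate would be 1 to 5 short per arm. If losses to follow-up catch every explained exit, the share not counted is zero and so is the shortfall. On direction: true 20% with half uncounted is reported as 10%, so apparent retention rises from 80% to 90%.

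**4. Safety statements side by side.** Section 2.3 records all events during sessions, with no attribution condition. Table 4 assesses events at start, end and close-out, also with no condition. Section 2.5.6 covers the whole trial but counts only attributable events. Collection is therefore wider than the reported measure, and the three statements do not share one scope.

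**The case against.** The strongest reply is that retention does not rest on the dropout count alone. The sentence that introduces it also counts losses to follow-up, adherence is tallied separately, and the participant-flow figure, which is not shown, may list explained exits. This stands in part. It makes understatement possible rather than certain, and it rules out saying that stops for injury are sure to go uncounted. It does not rescue the definition: a person who explains, stops and still attends visits fits neither term.

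On safety, the reply is that the passages complement each other. A reader might infer that events are collected only during sessions, or that a delayed injury or fall is excluded. The text supports neither. Section 2.3 does not limit recording to sessions, and a delayed injury judged attributable falls within the Section 2.5.6 measure. The restriction is on what is reported. How relatedness is judged may be set out in the full protocol, and its absence here is not part of this point.

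A reader might also infer that the full-scale trial will be sized on these figures. Section 2.4.1 speaks of preliminary data in general, while justifying the primary outcome, and names neither retention nor safety. The link is an inference from Section 2.2.2, where attrition is an input to the sample size.

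Nor does anything show that people who stop exercise are barred from later visits. They are discontinued from the intervention, and Section 2.6 applies intention-to-treat to the primary outcome.

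**Conclusion.** The point holds in a limited form. As written, the dropout rule omits explained withdrawals, people whom staff reach, and protocol discontinuations, and it follows attendance rather than the endpoint. Attrition may be understated and retention correspondingly overstated. The reported safety measure is narrower than what is recorded, so harm may be understated in that measure, and Sections 2.3, 2.5 (Table 4) and 2.5.6 must be reconciled.

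No size can be derived from the documents. The shortfall of 1 to 5 per arm rests on assumed true attrition of 10% to 25% and on 25% to 75% of exits escaping both counts; it falls to zero if losses to follow-up are defined to include them. Nothing here shows that the trial's own sample size is wrong or that its primary analysis is compromised. The change is worth making because attrition and safety are listed outcomes and the correction is cheap.

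**What to change.** - Define attrition as every randomised participant without an evaluable end-of-intervention stool sample, whatever the reason, and likewise at close-out. Report it by arm.
- Report separately, by arm and with reasons, everyone who stopped exercise, including discontinuations under Section 2.3. If the present rule is kept, label it as unexplained loss of contact, and define loss to follow-up.
- Report all recorded adverse events by arm, with relatedness as a descriptor and not a condition for being counted. Give Section 2.3, Table 4 and Section 2.5.6 one stated scope.

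The cost is definition wording and one case-report-form field for the reason. The design and sample size are untouched. The small downside is a higher reported attrition and event count.
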